#### NR Supplement dose and rationale for dose selection

We will use 300 mg tablets of the supplement nicotinamide riboside (NR) (Tru Niagen®, ChromaDex, Irvine CA) which is the formulation used in previous well-controlled pharmacokinetic/pharmacodynamic and interventional studies [19, 41]. NR is a form of vitamin B3, a precursor for NAD^+^ [14]. NR is available as a dietary supplement and is generally recognized as safe (GRAS) by the FDA.

The “no adverse effect level” of NR proposed by the European Commission Scientific Committee on Food was 25 mg/kg per day, and the conservative tolerable upper intake level proposed was 12.5 mg/kg per day, or 900 mg for adults [42]. In adults, doses of 100, 300, and 1,000 mg of NR achieve dose dependent increases in the blood NAD^+^ metabolome [41], thus we propose to use the tolerable upper intake level, 900 mg, as the maximum dose for adults, and corresponding doses (in proportion to body weight) in children. We will use the following doses:For individuals with weight 72 kg: 900 mg po qd × 16 wks.For individuals with weight 48 to < 72 kg: 600 mg po qd × 16 wks.For individuals with weight 24 to < 48 kg: 300 mg po qd × 16 wks.

This regimen achieves a maximum dose of 12.5 mg/kg/day (24 kg is ~ 3rd%ile for weight for a 10yo child, thus this weight threshold is more than sufficient for adolescents ages 15y and older to enroll). In a previous pediatric study, ~ 1,200 mg/m2 of nicotinamide for 5y was well-tolerated, more than what is proposed here [21] {11a}.

A concurrent use of any medication that likely increases the risk of NR toxicity is not permitted for all participants during the study period. Furthermore, those who are using such medications will be excluded from the study {11d}.

### Data management {19}

The study team will work with Data Management CHOP CHPS Informatics Core to generate case report forms and design a REDCap database for data capture. REDCap is an NIH-supported web-based data management software designed by Vanderbilt University investigators.

The PI is responsible for the accuracy and completeness of data collection and management. The PI may designate qualified individual(s) to collect data and manage data. Only investigators and research staff that have completed appropriate IRB training and approval and are listed on the IRB approved protocol are eligible to collect and work on information from the study. Future studies that may use patients or data collected from this study must have separate approved IRB protocols and consent forms, if applicable. Partial or complete datasets will be provided depending on the stated purpose of each data request. Only de-identified data will be shared. We will make the data available to users only under a data-sharing agreement that provides for:commitment to use the data only for not-for-profit research purposes;commitment to maintain the data in a secure environment;commitment to protect the privacy and identity of study participants and not to identify any individual participant;commitment to securing the data using appropriate computer technology;commitment to destroying or returning the data after analyses are completed;commitment that the data will not be transferred to other users;commitment to maintain all appropriate regulatory requirements;commitment to acknowledge the source of the data (NIH grant support and research team) in all publications and presentations.

It is the goal of this research team to translate the study findings into clinical care in order to impact the health and well-being of children. To that end, it is the intention of the research team to communicate the results of this study to the scientific community as rapidly as possible, and to share data as openly as possible {31a}.

Recruitment data will be recorded onto the screening questionnaire. Original data will be recorded directly onto CRFs by the study coordinator or a study investigator. Copies of testing results will be received through inter-office mailing, picked up directly, and sometimes through email. This information also will be recorded onto CRFs while the originals may be kept at the testing site. CRFs will be kept in a locked filing cabinet in a locked room at all times (study coordinator and/or PI office). All information will be transferred to REDCap, a secure, web-based application supported by the CHOP Research Institute. The password to log onto the database will be unique to each member of the study team. Information may also be stored in Oncore Clinical Trials Management System, a secure electronic data capture system with access controls and a data back-up plan. The system is password protected. Only study team members will have access to study data and case report forms stored in OnCore. Access to the system is monitored and logged for review, if needed {29}. The identifiable information collected as part of this study will be retained for a duration that is compliant with CHOP Data Retention Policy A-3–9 {31c}. Blood specimens will be retained indefinitely, as subjects will consent to during informed consent. The PHI linked to these specimens will remain coded and accessible only to IRB-approved study staff {27}.

Once a year, the division of Oncology at the CHOP will audit the study. Additionally, the CHOP IRB will, at random, select the study for an internal audit. The study will follow the institutional guideline to ensure that it meets the regulations and is prepared for both an internal and an external audit {23}.

### Harms management {22}

Safety will be monitored through the collection of laboratory assessments at baseline and follow-up. Participants will also be monitored using a standardized assessment of symptoms. We will use the Common Terminology Criteria for Adverse Events (CTCAE, version 5.0, U.S. Department of Health and Human Services) to grade AEs. Individuals who experience a new Grade 3 or higher AE that is at least possibly related to the study intervention may require cessation of study participation at the discretion of the investigative team. Grade 4 AEs will require study cessation of study participation.

If any unanticipated problems related to the research involving risks to subjects or others happen during the course of this study including serious adverse events (SAE), they will be reported to the IRB in accordance with CHOP IRB SOP 408: Unanticipated Problems Involving Risks to Subjects. AEs that are not serious but that are notable and could involve risks to subjects will be summarized in narrative or other format and submitted to the IRB at the time of continuing review. All AEs will be noted in the study records and on the case report form with a full description including the nature, date and time of onset, determination of non-serious versus serious, intensity (mild, moderate, severe), duration, causality, and outcome of the event. An AE is defined as any untoward medical occurrence in a subject who has received an intervention (drug, biologic, or other intervention), and an SAE is defined as any adverse drug experience occurring at any dose that results in death, in a life-threatening event, in a persistent or significant disability/incapacity, or a congenital anomaly/birth defect in the offspring of a subject. The occurrence does not necessarily have to have a causal relationship with the treatment. An AE can therefore be any unfavorable or unintended sign (including an abnormal laboratory finding, for example), symptom, or disease temporally associated with the use of a medicinal product, whether or not considered related to the medicinal product.

The Safety Monitoring Uniform Report Form (SMURF) will also be used to assess NR specific side effects and will be administered at each in-person visit. The full SMURF contains a general inquiry, several questions about daily activities (e.g., sleep, appetite, energy level, bowel and bladder function), and modified queries specific to NR side effects. The general inquiry includes an open-ended question about any problems or complaints, as well as questions regarding the need for other medications and doctor or health care encounters since the last study visit. The next section includes 25 system-specific queries to ensure completeness. All new AEs will be documented. We will also check on the status of any previously reported possible AEs.

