**Methods/design:**

We will perform a randomized controlled trial testing 16 weeks of in-home aerobic and resistance exercise and NR in AYA HCT survivors, with a primary outcome of muscle strength via dynamometry and a key secondary outcome of cardiovascular fitness via cardiopulmonary exercise testing. We will also test the effects of these interventions on i) muscle mass via dual energy x-ray absorptiometry; ii) muscle mitochondrial OXPHOS via an innovative non-invasive MRI-based technique, and iii) circulating correlates of NAD^+^ metabolism via metabolomics. Eighty AYAs (ages 15-30y) will be recruited 6–24 months post-HCT and randomized to 1 of 4 arms: exercise + NR, exercise alone, NR alone, or control. Outcomes will be collected at baseline and after the 16-week intervention.

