### Study assessments {18a}

All study participants will complete a review of medical history, have their vital signs measured, and have laboratory assessments (CBC, CMP, HbA1c, lipid profile, blood to be banked for future ancillary metabolic and/or hormonal studies) (Table 3). Activity monitoring will be reviewed for seven days via an activity monitor (ActiGraph wGT3X-BT; ActiGraph Corp., Pensacola, FL) and, if assigned, the exercise training orientation will occur. After all study procedures are completed, supplement/placebo (NR/placebo) will be provided to the participant along with instructions and administration log. Specific to the primary and secondary outcomes, all participants will undergo the following assessments at the baseline and follow-up visits:

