### Statistical considerations

Linear mixed-effects modeling will be used to evaluate effect of interventions over time on the primary and key secondary outcomes. The models incorporate subject-specific random effects to account for within-subject correlation due to repeated measures. Group averages, as well as subject-specific intercepts and slopes, will be estimated to capture potential variations in the baseline values and slopes among individuals. Linear mixed-effects models accommodate missing data due to dropout, such that all randomized participants can be included. We will compare participants who complete the study with those who do not and identify potential factors that are associated with dropout {20c}. In the mixed-effects models, we will adjust for time-invariant covariates (age at randomization, sex) and time-varying covariates (muscle strength, lean mass, muscle OXPHOS capacity, VO2max). By including these indices of “muscle quality” as covariates in the models, we will be able to assess whether intervention effects are explained by these effects. To assess other potential factors influencing outcomes, we will also analyze the incremental effect of adding each of the other measured covariates (final dose of NR achieved, final training intensity achieved) to the models.

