The primary outcome for our study is the change in muscle strength (quadriceps extension, Z-score) from baseline to 16 weeks. We expect exercise and NR to each produce an increase (relative to control/placebo) with respect to the primary outcome of muscle strength from baseline to week 16. We posit that the effects of exercise and NR in combination will be additive and possibly even synergistic. Despite our strategies to track and optimize adherence, it is possible that the change in Z-score will vary across participants in response to one or both interventions. We will fit a linear model with the outcome of change in Z-score of muscle strength and covariates of treatment arm and baseline Z-score. Using a modification of previous strategies for the analysis of factorial designs, the family-wise Type I error rate is maintained at < 5% by using a two-stage approach: a Holm-Bonferroni correction is applied in Stage 1, and a single contrast is pre-specified in Stage 2 [43]. In Stage 1, we will test if the mean Z-score in each of the 3 active treatment arms differs from control (no-exercise + placebo). In Stage 2, if the exercise + NR arm differs from the control arm, we will then compare exercise + NR to exercise alone, to determine whether NR increases mean Z-score beyond the effect of exercise alone; 95% confidence intervals will be determined for each effect of interest.

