With regards to ensuring adherence and compliance to the intervention, our team will be monitoring study participants in real-time via regular telephone check-ins and for those participating in exercise, via remote oversight, and thus be well-positioned to troubleshoot any barriers that may emerge during the conduct of the study. For NR/placebo, the investigative team will interview the adherence and intervene where necessary to ensure consistent administration of NR/placebo. Barriers to adherence can be reviewed at weekly check-ins and the interim visit. With regards to the exercise intervention, in-person orientation at the study site to exercise training using the in-home equipment will occur on the day of randomization, thus any functional or logistical limitations can be addressed in real time. To improve retention, we will offer participants randomized to the “no exercise” condition the opportunity to participate in in-home training after completion of the study {30}. Subjects who withdraw from the study will be recommended to update their medical history/concomitant medications, undergo physical exam, measure vital signs, test their clinical labs, get a DXA scan, get a 60 min MRI, perform a CPET, provide used/unused NR or placebo, and review adverse events as the early termination visit if both safe and feasible {18b}. In our team’s previous two studies of remotely supervised exercise interventions, we have demonstrated adherence rates exceeding 80% using similar procedures {11c}.

We will apply the insights gained from this trial to develop individualized, evidence-supported precision initiatives that will reduce chronic disease burden in high-risk cancer survivors. Our proposed trial is an important first step and will guide future interventions. We may also find that the benefits that accrue to skeletal muscle in response to skeletal muscle-focused interventions are recapitulated in other organ systems. For example, NAD^+^ precursors have impact on cardiac muscle, tissue that can also be adversely affected in cancer patients; in a preclinical model of dilated cardiomyopathy, NAD^+^ precursor attenuated the development of heart failure [50]. Additional metrics, such as circulatory power at peak exercise, can be measured to provide a non-invasive estimate of the circulatory system (i.e., heart rate, stroke volume, and systemic blood pressure) at peak exercise to explore such potential benefits.

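### The adverse-event rule ends study participation rather than only the intervention, and nothing shown keeps these participants for week-16 strength testing

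*Protocol article*

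**What the plan says.** Harms management {22} sets two rules. The first covers "Individuals who experience a new Grade 3 or higher AE that is at least possibly related to the study intervention"; such a case "may require cessation of study participation at the discretion of the investigative team". The second is mandatory: "Grade 4 AEs will require study cessation of study participation". Both act on participation in the study. The section has no separate provision for stopping the supplement or the exercise programme while outcome assessment continues.

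The primary outcome is the change in quadriceps strength Z-score from baseline to 16 weeks. Statistical considerations gives its model: "We will fit a linear model with the outcome of change in Z-score of muscle strength and covariates of treatment arm and baseline Z-score". The same section says of dropout: "Linear mixed-effects models accommodate missing data due to dropout, such that all randomized participants can be included". It also plans to compare participants who complete the study with those who do not.

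On timing, the abstract says "Outcomes will be collected at baseline and after the 16-week intervention". Study assessments {18a} says "all participants will undergo the following assessments at the baseline and follow-up visits", and Methods/design places on-site visits at baseline, week 8 and week 16.

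For people who withdraw, the Discussion recommends an early-termination visit where safe and feasible. After history, examination, vital signs and laboratory tests, its list continues: "get a DXA scan, get a 60 min MRI, perform a CPET, provide used/unused NR or placebo, and review adverse events". Dynamometry is not in the list.

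**The concern.** Stopping an intervention for safety and leaving the study are separate decisions, and the rule merges them. Someone who has to stop NR or exercise may still be able to do an isometric knee-extension test safely at week 16. Under the rule as written, that person leaves and the primary outcome is not collected.

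This missingness would be triggered by a severe health event, so it may well be related to the outcome. It may also differ by arm, by two routes:

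- **Discretion.** Participants and randomization says that the study team knows the exercise assignment. Decisions to remove someone after a Grade 3 event could differ between exercise and no-exercise arms.
- **Event rates.** If exercise or NR changes how often qualifying events occur, exits will differ by arm even when nobody knows the assignment. Blinding does not prevent this, so the NR contrasts are exposed too.

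At stake is how far the primary comparison represents everyone randomised, which is the stated aim for the mixed models.

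**Working it through.** **1. What happens to the primary value.** Take a participant removed under the rule at week 6.

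- Change-score model: it needs a week-16 Z-score. Without one there is no outcome, and the participant drops out of the model.
- Mixed model: the participant can stay in, but only with the strength values already collected. The abstract implies baseline only. The wording on follow-up visits leaves a week-8 test possible, but removal at week 6 precedes it. Inclusion then rests on a missing-at-random assumption with little or no post-baseline strength data.
- Early-termination visit: it is recommended rather than required, falls at withdrawal rather than at week 16, and its listed tests do not measure the primary outcome.

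**2. The plan's own numbers.** Sample size and power: 64 complete / (1 − 0.20) = 80 randomised, which reproduces the stated figure. Per arm this is 20 randomised and 16 complete, so four losses are allowed. Each adverse-event exit uses one of the four. No adverse-event rates are given, so the number of exits cannot be estimated.

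**3. Would keeping these participants raise power?** The SD of the change score is not stated. Back-solving from 80% power for 0.73 Z at 16 per arm (two-sided 5%, normal approximation, single contrast, Stage 1 condition ignored):

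SD = 0.73 / [(1.960 + 0.842) × √(2/16)] = 0.737; SE = 0.737 × √(2/16) = 0.261.

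Suppose k more participants per arm are tested after stopping and keep a share r of the effect. The expected difference is 0.73 × (16 + k·r)/(16 + k), and the SE is 0.253 for 17 per arm and 0.246 for 18.

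| k per arm | r = 0 | r = 0.5 | r = 1 |
|---|---|---|---|
| 1: difference, power | 0.687, 77.6% | 0.709, 80.0% | 0.730, 82.3% |
| 2: difference, power | 0.649, 75.2% | 0.689, 80.1% | 0.730, 84.4% |

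Break-even is r = [√(16 × (16 + k)) − 16]/k, which is 0.492 for k = 1 and 0.485 for k = 2. Power rises only if about half or more of the effect is retained.

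**4. What drives the bias.** For an unadjusted comparison of those retained, bias = p1·g1 − p0·g0. Here p is the share removed in an arm, and g is the mean change in those retained minus that in those removed. If p and g are equal across arms, the bias is 0. The document gives neither quantity. Purely to show scale, assume equal g and 1 to 2 more exits per 20 in one arm:

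- 1/20 × 0.5 Z = 0.025 Z, or 0.025/0.261 = 0.10 SE
- 2/20 × 1.0 Z = 0.10 Z, or 0.10/0.261 = 0.38 SE

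These inputs are assumptions. The planned models also adjust for baseline, which this formula does not.

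**The case against.** The strongest reply is that this is a condensed article. The full protocol and Table 3 are not shown, and either could provide for continued follow-up or for dynamometry at exit. The Grade 4 sentence is also clumsily worded, so its exact phrasing can bear only limited weight. This stands to the extent that a reader might infer that removed participants certainly have no week-16 strength value; the document does not establish that. It does not dispose of the point, because the article states a rule that acts on study participation and nothing shown offsets it.

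Second, there are mitigations: the recommended exit visit, mixed models, a 20% attrition allowance, and discretion under the Grade 3 rule that already lets the team keep a testable participant. They help in part. The allowance protects precision but not against outcome-related missingness, a mixed model does not collect a value, and the Grade 4 rule leaves no discretion.

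Third, ending research procedures after a Grade 4 event in recent transplant survivors, some of them minors, is a defensible safety choice. That is accepted: the triggers can stay, and unsafe testing should be exempt.

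A reader might also infer that blinding to NR protects exercise + NR versus exercise. It limits removal based on knowledge of the assignment, but it does not equalise exits if NR itself changes event rates. The protocol also allows the investigator to be unblinded for some serious events.

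Finally, a reader might infer that any Grade 4 event counts, related or not. The sentence carries no relatedness condition, but one may be intended from the sentence before it. The point holds under either reading.

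**Conclusion.** The point holds in limited form. As written, the rule ends participation for Grade 4 events and, at the team's discretion, for possibly related events of Grade 3 or higher. Nothing shown secures the week-16 primary measurement for those affected. Missing outcomes could therefore depend on adverse events and on arm. Discretion by staff who know the exercise assignment bears on exercise versus no-exercise contrasts, and differing event rates could bear on NR contrasts as well.

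The number affected is unknown and probably small. The bias figures in the working should not be read as an estimate: they rest wholly on assumed exit differences and outcome gaps, and the bias is zero if exits and their outcomes are alike across arms. Nor is this a power argument, since the effect on power can go either way. The case is one of validity: fewer missing primary outcomes, and an analysis closer to all randomised participants. Severity is low to moderate.

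**What to change.** Reword Harms management so that an event meeting the criteria stops NR/placebo and/or exercise, while the participant stays in follow-up and attends the remaining scheduled assessments, including week-16 knee-extension dynamometry, unless testing is unsafe or consent is withdrawn. The grade and relatedness triggers remain the sponsor's decision, though it would help to say whether the Grade 4 rule requires relatedness. Add dynamometry to the early-termination visit for those who do leave. Values collected after stopping should be available to the all-randomised analysis; their exact handling can be set in the SAP.

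The cost is a few protocol sentences and matching consent wording. The week-8 and week-16 visits are already planned for every participant. The downsides are that off-treatment values may dilute the observed effect slightly (in the working, power for 0.73 Z falls to between 75% and 78% if none of the effect is retained) and that few values may be recovered, because some participants will not be fit to test.

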## Methods/design

In this randomized controlled trial, we will prospectively enroll 80 participants status-post HCT at two sites, the Children’s Hospital of Philadelphia (CHOP) (Philadelphia, PA, USA) and the City of Hope Medical Center (COH) (Duarte, CA, USA). There will be 4 arms: exercise intervention with NR supplementation, exercise intervention with placebo, no exercise intervention with NR supplementation, and no exercise intervention with placebo. The individualized exercise intervention will occur in the home, overseen remotely via Telehealth by exercise intervention physiologists from St. Jude Children’s Research Hospital (Memphis, TN, USA) {9}. Participants who are randomized to the exercise intervention will be given the necessary equipment to participate either before they depart the site or by mail. Each participant will take part in the study for 16 weeks, with a total of three onsite in-person visits: one at baseline, one interim visit at week 8, and a final visit at the end of the 16-week intervention.

The primary objective of this study is to measure the effect of combination administration (NR + exercise) on skeletal muscle quality (strength along with mitochondrial OXPHOS capacity) in AYA HCT survivors {7}. Skeletal muscle quality will be measured by dynamometry, while OXPHOS capacity will be assessed through creatine chemical exchange saturation magnetic resonance imaging (CrCEST MRI). The secondary objective of this study is to measure the effect of combination administration (NR + exercise) on aerobic capacity (VO_2_max), as determined by cardiopulmonary exercise testing (CPET).

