### Participants and randomization

Potentially eligible participants will be identified and recruited both at CHOP and COH through existing databases and physician referrals. Study staff will pre-screen potential participants by reviewing the medical charts and exclude those who do not meet inclusion/exclusion criteria {15}. Individuals who meet the eligibility criteria (Table 2) will be invited to enroll. All participants will be enrolled when they provide written consent to the principal investigator(s) either virtually or in-person and all the initial eligibility requirements are met {26a}. Once eligibility is confirmed via in-person screening procedures, participants will be randomized into one of four arms, with randomization stratified by age (≥ 18y or < 18y) and site (CHOP or COH) by a designated study member using REDCAP randomization scheme (Fig. 2) {16b} {16c}. Balance between arms will be maintained through randomly permuted blocks of size four or eight {16a}. The research team, outcomes assessors, care providers, and participants will be blinded with respect to whether participants are receiving NR vs. placebo. NR and placebo are dispensed in identical capsules to avoid un-blinding. The outcomes assessor (but not the study team, care providers, or participants) will be blinded with respect to whether individuals are receiving the in-home exercise intervention vs. no exercise intervention {17a}. The Investigator will be unblinded only if an AE occurs that is determined to be serious, and treatment for the adverse event (AE) depends on knowing the group assignment. Participants/families will be unblinded at the completion of the entire study {17b}. The current study has been approved by the Institutional Review Board of Children’s Hospital of Philadelphia (approval number: IRB #17,320) and has been pre-registered at www.clinicaltrials.gov (NCT05194397). The Standard Protocol Items: Recommendations for Interventional Trials (SPIRIT) guideline was used to generate the report [27].

**Table 2 Tab2:** Inclusion and Exclusion Criteria {10}

Inclusion Criteria	Exclusion Criteria

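### The SAE definition is worded for drug experiences only, at odds with the wider AE definition beside it, and does not list hospital admission

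*Protocol article*

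**What the plan says.** Harms management {22} gives both definitions in one sentence. For AEs: "An AE is defined as any untoward medical occurrence in a subject who has received an intervention (drug, biologic, or other intervention". For SAEs: "an SAE is defined as any adverse drug experience occurring at any dose that results in death, in a life-threatening event", and the list then finishes with "in a persistent or significant disability/incapacity, or a congenital anomaly/birth defect in the offspring of a subject". Nothing in the sentence leaves the list open, and no other section adds a criterion.

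The next sentence reads "The occurrence does not necessarily have to have a causal relationship with the treatment". The one after it returns to AEs and describes them as events "temporally associated with the use of a medicinal product, whether or not considered related to the medicinal product".

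Participants and randomization sets the emergency unblinding rule: "The Investigator will be unblinded only if an AE occurs that is determined to be serious", with the further condition that treatment of the event depends on knowing the assignment.

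Methods/design lists the four arms as "exercise intervention with NR supplementation, exercise intervention with placebo, no exercise intervention with NR supplementation, and no exercise intervention with placebo". Every participant therefore takes capsules, and the two exercise arms also receive the home programme.

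**The concern.** Two things look wrong. First, the SAE wording speaks of a drug experience and a dose in a trial where one of the two factors is exercise and where the assessments include symptom-limited cardiopulmonary exercise testing. The AE wording beside it has no such limit, so an event can fall plainly within the first definition and only doubtfully within the second. Two sites could code the same event differently.

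Second, the list omits hospital admission. These participants are 6 to 24 months past allogeneic transplant for acute leukaemia. An admission that does not kill, threaten life or disable is non-serious on the text as written.

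The classification matters because other rules depend on it. It is recorded for every AE, it affects when the IRB is told, it determines which listing the DSMB reads, and it appears to be the gate for unblinding. The article also says that the safety data will help guide clinicians whose patients consider the supplement.

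**Working it through.** No figure in the plan bears on this point, so there is nothing to recompute. The check sets the provisions side by side.

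1. **Scope of the two definitions.** An AE is "any untoward medical occurrence in a subject who has received an intervention (drug, biologic, or other intervention", which includes exercise. An SAE is an adverse drug experience at any dose. As worded, the SAE is not simply an AE that meets a seriousness criterion; it is a narrower kind of event. The two scopes do not match.

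2. **Does the causality sentence close the gap?** Partly. It follows the SAE definition directly and says that no causal link is needed, and all four arms take NR or placebo. A fatal, life-threatening or disabling exercise event in someone taking capsules can therefore be read as an SAE. The reading is not secure, because the sentence after it draws its conclusion about AEs, not SAEs. The wording is ambiguous; it does not exclude these events.

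3. **Events before the first capsule.** Study assessments {18a} provides the capsules once the study procedures are done. A serious event at baseline exercise testing comes before any dose, so it is hard to call a drug experience. The AE definition also presupposes that an intervention has been received, so it too reaches such an event only if the test itself counts as an intervention.

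4. **An admission under the four criteria.** Take a participant admitted, treated and discharged, with no threat to life and no lasting disability:
   - death: no
   - life-threatening: no
   - disability or incapacity: no
   - birth defect: no

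   The event is non-serious, whichever of the four arms the participant is in.

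5. **What follows from that code.**
   - *IRB.* Unanticipated problems involving risk, including SAEs, are reported under the IRB's procedure. Notable AEs that are not serious wait for continuing review. The admission goes by the second route unless it is reported as an unanticipated problem.
   - *DSMB.* The closed-session report lists AEs and SAEs by arm (Appendix, Meeting materials). The admission appears, but only among the AEs.
   - *Unblinding.* The rule needs an AE determined to be serious and treatment that depends on the assignment. If serious has the Harms management meaning, the first condition fails however strongly the second is met. Exercise allocation is already open to the study team, care providers and participants, so only the NR-versus-placebo code is at issue.

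6. **Size.** The omission applies to 4 of 4 arms, that is, to all 80 participants planned. The article gives no rate of admissions or serious events, so neither a number of misclassified events nor a difference between arms can be derived.

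**The case against.** The best answer is that little is lost. Admissions can still be picked up as AEs, because the safety questionnaire asks about contacts with health care at each in-person visit. AEs are graded by CTCAE, and the Grade 3 and Grade 4 provisions do not depend on seriousness. The IRB trigger is wider than SAEs. The DSMB receives AEs by arm, and no separate rapid SAE route to it is described that could be missed. The unblinding sentence does not use the term SAE or refer to the list, so an investigator might judge an admission serious on other grounds. All of this stands. It shows that the problem is one of classification and timing, not of capture. It does not make the admission serious or give the word one meaning.

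It can also be said that an article condenses a fuller protocol. That would answer a missing definition. Here the article states one, in full and as a closed list.

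A reader might go further and infer that serious exercise harms are not SAEs, so that the two exercise arms, 40 of 80 people under equal allocation, lie outside the definition. The documents do not support this: capsules are taken in every arm and no causal link is asked for. Nor do they support an undercount that is greatest in the exercise arms, since no event rates are given. It would also be wrong to call the exercise unsupervised. Methods/design and the exercise section describe remote oversight by exercise physiologists, with supervised sessions that taper over the 16 weeks.

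**Conclusion.** The point holds in limited form. The SAE definition conflicts in scope with the AE definition in the same sentence, which leaves the status of serious exercise and procedure events ambiguous. It also omits hospitalisation, so that in any of the 80 participants an admission without one of the four listed outcomes is coded non-serious, with the consequences for the IRB, the DSMB listing and possibly unblinding set out above.

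Two assumptions carry the result: that the four outcomes are meant as a complete list, as the sentence reads, and, for unblinding only, that serious means the same in both sections. The efficacy analysis is not affected. The change should be made because safety classification depends on it and the cost is small.

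**What to change.** - Define an SAE as any AE, whatever its cause (NR or placebo, exercise, or a study procedure), that meets a seriousness criterion, and drop the drug-and-dose wording.
- Add inpatient hospitalisation, or its prolongation, to the criteria.
- Reconcile the AE definition with this, stating whether events at baseline testing before the first capsule are covered.
- Reconcile the unblinding sentence in Participants and randomization with the definition, so that serious has one meaning. Which clinical circumstances justify unblinding is for the investigators to settle; the statistical need is only that the two sections agree.
- Carry the same definition into the serious/non-serious field on the CRF and into the DSMB report templates.

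The cost is protocol and CRF wording and somewhat more SAE forms. Sample size, randomisation and the planned analyses do not change.
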